### Assignment of interventions

#### Randomization

Random allocation is stratified by center [45]. Patients are assigned to intervention or control group in the study after the eligibility criteria are met. The randomization is performed by following a list of random allocation generated by computer, by the project manager. The unit of randomization is then the patient since the enrollment in the study begins with the patient. However, to limit the risk of contamination due to the fact that a RP can have several patients included in the study, patients with the same RP will be allocated to the same study group. Specifically, each patient coming in geriatric or memory consultation and whose the RP was not identified for a patient previously included, will be assigned randomly to one of the study groups: intervention, or control. Patient will be enrolled by the geriatric/neurologist doctor during the consultation. When a new patient has the same RP that a patient previously enrolled in the study, this new patient will automatically be assigned to the same study group as the previous patient. Finally, the number of patients per RP will be limited to 4.

#### Blinding

The study is considered as open-label. The PI will perform the clinical medical review for all patients included in the study, regardless of their allocation group. Patients and RP will be aware of group allocation by the nature of the intervention which may lead to changes in their drug prescriptions. However, as the primary outcome is evaluated among the patient and by its nature, we assume that the knowledge by patients of their allocation group in the study will have little or no impact on the evolution this outcome.

### Data collection, management, and statistical analysis

#### Data collection methods and data management

The clinical data are collected in a case report form (CRF) assigned to each patient, referred by a unique numeric identifier, using the patient medical record and during the consultation, by a trained neuropsychologist or nurse. Primary and secondary outcomes are collected during the assessment at the consultation. Data are then entered into a computerized database by the neuropsychologist or the nurse. Drugs are collected by the clinical pharmacist using the RP prescriptions and those of the specialist physician at hospital after the consultation. Drugs data and pharmaceutical analysis and PI are entered in the computerized database by the clinical pharmacist. The data collected in the CRF and in the database will be verified for accuracy, missing data, and data consistency with the documents ‘source’ (medical records, visits schedules). Data quality will be analyzed during the study. The completeness and the information will be checked for plausibility in each case report form by a clinical research associate (CRA).

#### Statistical analysis

The analyzes will be performed with an intention-to-treat principle, both RP-patients will remain in their group allocation determined by the randomization procedure, regardless of the nature of the intervention that may have been applied during the study. Analysis per protocol will be performed to verify whether the results are similar with the two approaches. The presence of missing data and extreme values will be verified [46]. Missing data on the primary outcome may be taken into account to some extent in the statistical models used. The impact of missing data on the results will be evaluated as appropriate.Statistical analyzes will be performed using SPSS software (version 19.0, SPSS Inc. statistics). The analyses will focus on data at the patient level and statistical models will take into account possible correlations between data, such as the RP who can be considered as a hierarchical level above the patient unit [47]. The choice of tests will also be adapted to the nature of the variables, and based on the assumptions for the application testing. The significance level for the tests performed on the primary outcome will be 0.05. This threshold will be adjusted for multiple comparisons and sub-analyzes of secondary outcomes when appropriate (Scheffe, Bonferoni correction) [48]. The tests will be bilateral.

#### Descriptive analyzes

A flow-chart will be presented to describe the number of RP per study group, the number of patients selected at inclusion, and the number of patients being followed according to the terms of the protocol, and the loss of follow-up.

Patient characteristics will be compared between the participating centers. Patient characteristics will be compared between the included and followed patients in the study and patients loss of follow-up to assess possible bias. Patient characteristics at baseline will be described for the entire study population, and study group. Quantitative variables will be summarized by mean and standard deviation or median and percentiles if their distribution is not symmetrical. Categorical variables will be presented by frequencies and numbers.Comparisons will be made to test patient characteristics at baseline between the two allocation groups. Means will be compared using the Student *t* test or Mann-Whitney U as appropriate. The proportions will be compared using the chi-square test of two Pearson. The tests will be adjusted to the design effect of the study [49, 50].

#### Comparative analyzes to assess the impact of the intervention on the primary outcome

The ICC will be calculated on the primary outcome for the entire population and by groups to verify that the correlation between observations is similar between groups. The effect of the intervention on evolution of the level of autonomy function will be estimated in a generalized linear mixed model. The mixed model will account for both fixed and random effects, hierarchy data (patient characteristics correlated between them for a same RP) and repeated measurements of the primary outcome [51, 52]. The evolution of the primary outcome will be defined as the dependent variable, explained by the effect of the study group, the time effect and the interaction between these two effects. The intervention will be considered significant if the interaction between time and the study group is significant. The significance level of each term in the model will be presented. The coefficients associated with variables in the model, their 95% confidence interval and significance level will be presented. The effects of covariates will be tested in the model: recruiting center, age, sex, comorbidities, education level and estimates will be adjusted if the effects are significant to account for these confounders. The interaction between patient characteristics and study group will be tested one by one, and analyzes will be stratified if the interactions are significant and that the result is considered clinically relevant.

The impact of the intervention on the secondary outcomes will be investigated using generalized linear mixed models. To explain the dependent variables, other models such as nonlinear mixed effects models or Cox model will be used [53].

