### Participant timeline

The OPTIM study is part of the routine care of patients at geriatric/memory center. Four successive evaluations are planned for the participants (Table 1). The inclusion is planned at the first consultation of the patients at the geriatric/memory center. Three others evaluations during follow-up are planned: at 1 month and after 6 months and 18 months. At 6 and 18 months, the patients will undergo a consultation at the geriatric/memory center, whereas the limited evaluation at 1 month will be performed by phone with the primary caregiver.

**Table 1 Tab1:** Schedule of enrolment, intervention and assessments of the OPTIM study

	Study Period				
	Enrolment	Allocation	Follow-up		
Timepoint	- *t1*	0	*t* _*1*_ *: 1 month*	*t* _*2*_: *6 months*	*t* _*3*_: *18 months - Close-out*
Enrolment:					
Eligibility screen	X				
Information to patients/careviger	X				
Collection of non-opposition to participate	X				
Randomized allocation		X			
Intervention:					
*(1) Intervention: Optimization of drug prescribing*		X	X	X	
*(2) Control*					
Assessments:					
*Collected in patient record:* * Sociodemographic data * Diagnosis and stage * Current comorbidities, history of comorbidities, lifestyle habits * Biological exam and artrial pressure when available		X			
*Primary outcomes:* * IADL scale * DAD-6 scale		X	X	X	X
*Secondary outcomes:* * MMSE (cognitive function) * mini-GDS (depression) * Hamilton scale (anxiety) * Pain scale * EUROQOL-5D (quality of life) * Girerd scale (compliance to drug prescribing) * Event and date of event: hospitalization, falls, recourse of emergency, institutionalization, death		X		X	X
Drugs prescribing		X	X	X	X

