### Sample size

The number of subjects needed was calculated on the primary outcome (IADL) to demonstrate a significant difference in the evolution of functional activities between the intervention group and the control group. The IADL score in patients aged 70 years deteriorates on average of 16% over a period of 18 months. This evolution would represent a change of 1.3 percentage points (SD 2) expected in the control group in our study population. To highlight a 20% difference of the evolution of this score, equivalent to a change of 1.04 points of IADL in the intervention group, for an alpha = 0.05 and a power of 80% (two-tailed test), it is necessary to include 224 patients (112 per group). A first observation made in the Charpennes Hospital showed that RP referred 2 patients in average at the memory center. Taking the conservative assumption of 4 patients on average per referent physician, the inflation factor applied was 1.03 for an intra-class coefficient (ICC) of 0.01 [43, 44]. Taking into account the ICC, the number of subjects needed was 232 patients spread between the 2 study groups. Finally, the number of subjects required was corrected for an expected attrition rate of 25%; the corresponding correction factor was 1.3. Assuming that the rate is the same in the 2 groups, the number of subjects required was 302 patients.

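### The primary model does not adjust for the baseline IADL or DAD-6 score: under the natural reading the test is valid, but less precise than the collected data allow

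*Protocol article*

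**What the plan says.** All points are in the protocol article.

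- *Comparative analyzes to assess the impact of the intervention on the primary outcome* defines the response: "The evolution of the primary outcome will be defined as the dependent variable". The model terms follow: the response is "explained by the effect of the study group, the time effect and the interaction between these two effects". The decision rule is "The intervention will be considered significant if the interaction between time and the study group is significant".
- The same section gives the candidate covariates and the condition for keeping them: "The effects of covariates will be tested in the model: recruiting center, age, sex, comorbidities, education level and estimates will be adjusted if the effects" prove significant. Neither baseline score is listed, and no constraint on the groups' baseline means is stated.
- *Participant timeline*, Table 1, schedules the row "IADL scale * DAD-6 scale" at time 0 and at 1, 6 and 18 months.
- *Sample size* works with the difference in change: "This evolution would represent a change of 1.3 percentage points (SD 2) expected in the control group in our study population", against 1.04 points in the intervention group.
- *Descriptive analyzes* compares the groups at baseline by significance tests and attaches no adjustment for the baseline score.

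**The concern.** A patient's starting score is usually a strong predictor of the later score on the same scale. The model uses it as a first repeated measure but leaves each group its own free starting mean. The 18-month interaction then reduces to a comparison of raw changes, which carries all the noise of the baseline measurement. If the groups differ at baseline by chance, part of that difference also stays in the estimate through regression to the mean.

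What is at stake is precision and conditional balance, obtained from data the trial collects anyway. Adjusting for all five listed covariates would not recover it, because the baseline score is not among them.

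**Working it through.** **Inputs from the documents:** control change 1.3 and intervention change 1.04, so the target is 1.3 - 1.04 = 0.26 points; SD of change 2; two-sided alpha 0.05; power 80%; 112 per group; IADL range 0 to 8; visits at 0, 1, 6 and 18 months.

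**Assumed:** rho, the baseline-to-18-month correlation; equal score SD s at the two times; normal, complete data.

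**1. The plan's own figure.** n per group = 2 x [SD x (1.960 + 0.842) / difference]^2 = 2 x [2 x 2.802 / 0.26]^2 = 929, not 112. With 112 per group the standard error is 2 x sqrt(2/112) = 0.267. The difference detectable with 80% power is 2.802 x 0.267 = 0.75 points, and power at 0.26 points is about 16%. The stated 80% therefore serves below only as a reference point.

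**2. Variance ratio.** Per patient, the variance of raw change is 2s^2(1 - rho). The variance of the 18-month score given baseline is s^2(1 - rho^2). The ratio is (1 + rho)/2. A generalised least squares calculation on the four visits with categorical time, comparing free with common baseline means, gives the same ratio under exchangeable and autoregressive correlation.

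**3. Plausible rho.** An SD of change of 2 means 4 = 2s^2(1 - rho), so rho = 1 - 2/s^2. For s = 2.0, 2.5 and 3.0, rho is 0.50, 0.68 and 0.78. A score limited to 0-8 cannot have an SD above 4, so rho cannot exceed 1 - 2/16 = 0.875 if the variances are equal.

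**4. Effect on the 18-month contrast, 112 per group.** Adjusted power from 80% is Phi(2.802/sqrt(ratio) - 1.960).

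| rho | variance ratio | power from 80% | detectable difference | power at 0.26 (16% unadjusted) |
|---|---|---|---|---|
| 0.5 | 0.75 | 90% | 0.65 | 20% |
| 0.6 | 0.80 | 88% | 0.67 | 19% |
| 0.7 | 0.85 | 86% | 0.69 | 18% |
| 0.8 | 0.90 | 84% | 0.71 | 18% |

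**5. Other forms of the decision term.** The document does not say how time is coded.

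- *Joint 3-df interaction*, with a linear divergence reaching 0.75 points at 18 months. Exchangeable correlation: 76% rises to 82%, 79% and 78% for rho 0.5, 0.7 and 0.8. Autoregressive: 64.5% rises to 78%, 72% and 70%.
- *Linear time*, set to 80% unadjusted. Exchangeable: 85%, 83% and 82% for the same rho values. Autoregressive: 90%, 86% and 84%.
- *Variance growing over time* (random slopes; residual variance assumed to be 20% of baseline variance): 81% to 84%.

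The gain therefore runs from about 1 to 14 points. No case computed showed a loss.

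**6. Chance imbalance.** A baseline difference d leaves -(1 - rho)d in the change contrast. At rho 0.5 (s = 2), one standard error of the baseline difference is 2 x sqrt(2/112) = 0.27, and the shift is 0.13 points in absolute size. At rho 0.7 (s = 2.58), it is 0.3 x 0.345 = 0.10. The target is 0.26.

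**7. Change scores as the response.** With changes at 1, 6 and 18 months, the 18-versus-1-month interaction contrast is (Y18 - Y0) - (Y1 - Y0) = Y18 - Y1. Baseline cancels, and a baseline main effect leaves this contrast unchanged in complete data.

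**The case against.** The best defence is that this is a choice between two legitimate longitudinal models. Baseline already enters as the first repeated measure, so its absence from the covariate list is what one would expect. The free group term absorbs a difference in starting level, and the test is valid and unbiased over randomisations. All of this stands.

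Four stronger readings are tempting, and the document supports none of them:

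- *That the plan ignores baseline, or lets a baseline difference pass whole as a difference in evolution.* Only the fraction (1 - rho) of it remains.
- *That the point holds whichever response is meant.* The wording about evolution is ambiguous. With change scores, baseline drops out of the interaction (step 7), and the question becomes which term should be tested.
- *That power rises from 80% to 90%.* That needs rho 0.5, a single 18-month contrast and a starting power that the plan's own inputs do not give.
- *That the allocation rule makes chance imbalance large.* The clustering adds little: about 2 patients per physician, at most 4, with a design effect of 1.03. The rule matters in another way. Later patients of a physician join an arm already known, so forcing equal baseline means could be wrong if enrolment were selective.

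It can also be said that a condensed article may leave such detail to an analysis plan. But this article names the terms, the decision rule and the covariates, so an analysis plan that followed it would carry the omission forward.

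**Conclusion.** The point holds as a modest loss of efficiency and of conditional balance. It rests on reading the four scores as repeated responses with a free group effect. With categorical time, adjustment removes 10% to 25% of the variance of the 18-month contrast for rho between 0.8 and 0.5, assuming equal variances. The benefit in power depends on rho, the time coding and the correlation structure, none of which is stated.

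The shortfall in the sample size is separate and larger. At rho 0.5 the literal target would still need 0.75 x 929 = 697 per group, so baseline adjustment does not close that gap.

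**What to change.** In the primary-outcome analysis section, prespecify baseline adjustment for each primary scale, with that scale's own baseline score, kept regardless of significance. Two forms serve:

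- **Baseline as covariate.** Model the scores at 1, 6 and 18 months with the baseline score and its interaction with time as covariates. The decision term becomes the group difference at 18 months. The group-by-time interaction should not be kept for that role, because without the time-0 response it no longer measures change from baseline.
- **Common baseline mean.** Model the scores at all four visits with one shared mean at time 0. The decision term is the 18-month group-by-time term.

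Name one as primary and the other as a check. The common-mean form assumes comparable groups at time 0, and *Randomization* places later patients of a physician in a known arm. The covariate form does not impose equal means, but it omits patients without a baseline score.

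Use the same rule for secondary scales with a time-0 value (MMSE, EQ-5D, mini-GDS, Hamilton, pain, Girerd).

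The cost is a few sentences of analysis wording, with no new data, visits or patients.

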To limit the consequences of potentially harmful prescriptions, optimizing drug therapy is a major focus of improving quality and safety of care in the elderly. In a multidisciplinary team of healthcare providers, various pharmacist interventions can be implemented throughout the whole care process. The medication reviews are considered as a key element in improving the quality of prescriptions and in preventing ADEs among patient. There are three types of interventions: 1) prescription analysis, 2) adherence evaluation and 3) clinical medication review. The clinical medication review is defined as a structured, critical examination of a patient’s drug prescription with the objectives of reaching an agreement with the patient about their treatment, optimizing the impact of drugs, minimizing the number of drug related side effects rationalizing and simplifying drug regimens and reducing the iatrogeny. The clinical medication review included five interventions: medication history, review of current medication, pharmaceutical intervention, multidisciplinary review of drug prescriptions and medication liaison service (comprehension medication history, discharge letter transmitted to referent physician (RP) of the patient and community pharmacist, discharge counseling). Previous studies have found a positive impact of these interventions on the reduction of PIP, polymedication, adverse drug events in hospitalized elderly and in primary care [1, 30–32]. However, impact of such interventions by the clinical pharmacist integrated in a multidisciplinary approach has not been evaluated in terms of evolution of functional autonomy [33]. The evolution towards functional disabilities, frequent with aging, is at the heart of the concerns of public health authorities. Due to an increasing proportion of elderly in the population and the increase in life expectancy, the care-dependent patients increase the human and financial costs [34]. The evolution of loss of functional autonomy has many causes and risk factors, among which some could be prevented. Among these causes or risk factors, cardiovascular disease, stroke, type 1 or 2 diabetes, impairment of cognitive performance, sleep disorders, depression, a recent hospitalization and polypharmacy may have negative impact on functional autonomy [35, 36]. These observations from the literature make us assume the existence of an indirect link between inappropriate drug prescriptions and accelerated evolution to functional dependence, through suboptimal treatment of chronic diseases and greater frequency of adverse events. A literature review showed that the inappropriate prescription of drugs has a negative impact on functional status of patients; the most offending drugs are benzodiazepines, and anticholinergic drugs [37].

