### Outcomes

The primary outcome will be the evolution of patients’ functional autonomy level assessed with two scales: The Instrumental Activities of Daily Living (IADL) scale of Lawton and the 6-item Disability Assessment of Dementia (DAD-6) scale. Each scale will be analyzed separately. The evolution of functional autonomy will be calculated using the successive evaluations of the scales. The IADL scale assesses the level of functional autonomy of a patient through the assessment of instrumental activities of daily living including ability to use the telephone, transportation, shopping, managing medications, manage a budget, prepare meals, maintain the house and do the laundry. The rating scale provides a score from 0 to 8. A higher score indicates a higher level of dependency, while a lower score reflects a lower level of dependence. The IADL scale consists of 8 questions. The DAD-6 assesses the patient’s activities in his daily life. It includes six questions assessing the degree of autonomy for the following activities: Food, use the telephone or the computer, moving outside, finance and correspondence, medications, leisure and home maintenance. The score ranges from 0 to 18 points, the higher the score is, the more the patient is autonomous. The IADL and DAD-6 scales will be collected during an interview between the patient’s primary caregiver and a neuropsychologist, a nurse or a physician.

The secondary outcomes collected for patients will be the occurrence and the number of all-cause hospitalizations and all-cause emergency department visit after inclusion, admission in institution, and the delay before institutionalization, the occurrence and number of falls after inclusion, the overall cognitive function estimated by the Mini Mental Sate Examination (MMSE) [38] at baseline and its evolution assessed using the successive measures performed at each visit, the quality of life of the patients measured by the questionnaire EUROQOL 5D (EQ5D) [39], the depression and anxiety disorders measured respectively with the mini-GDS scale [40], and the Hamilton scale [41], the compliance of patients with treatment measured with the Girerd questionnaire [42], pain measured with an ordinal scale from 0 to 10, and the possible occurrence of all-cause death. The secondary outcomes collected for RP will be the number of PIP after intervention, and the type of DRP.

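### The primary model's covariate list leaves out baseline MMSE, giving up a modest amount of precision from data the trial already collects

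*Protocol article*

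**What the plan says.** The section on comparative analyses of the primary outcome describes a generalized linear mixed model with study group, time and their interaction. The decision rule is: "The intervention will be considered significant if the interaction between time and the study group is significant". The same section then names the candidate covariates: "The effects of covariates will be tested in the model: recruiting center, age, sex, comorbidities, education level". It makes their use conditional: "estimates will be adjusted if the effects are significant to account for these confounders".

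Four other places bear on this:

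- **Background.** Among causes or risk factors the article writes that "impairment of cognitive performance, sleep disorders, depression, a recent hospitalization and polypharmacy may have negative impact on functional autonomy". Cardiovascular disease, stroke and diabetes stand in the same sentence.
- **Outcomes.** A secondary outcome is "the overall cognitive function estimated by the Mini Mental Sate Examination (MMSE) [38] at baseline", followed by its later course. Table 1 schedules the MMSE at allocation, 6 months and 18 months.
- **Table 1.** "Diagnosis and stage" is recorded at allocation, on a line separate from comorbidities.
- **Randomization.** "Random allocation is stratified by center"; no other stratification factor is named.

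No reason is given for leaving MMSE off the list.

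**The concern.** The article does not leave covariates to a later plan. It prints a list and calls the items confounders. The list includes sex and education but no measure of cognition. Yet the trial recruits at geriatric and memory centers, one of its two primary scales is a dementia disability scale, and its own Background names cognition as a risk factor for functional loss.

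Nothing on the list stands in for MMSE. Both sites are geriatric and memory centers, so center does not separate patients by cognition, and a comorbidity count does not carry an MMSE score. The repeated IADL and DAD-6 measurements capture where a patient starts. They do not capture how fast a patient with a given level of cognition declines from there.

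Two things are at stake. Variation in the rate of decline that MMSE could explain stays in the error of the time-by-group term. And if the arms differ by chance in baseline cognition, the estimate is not corrected for it.

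**Working it through.** **Inputs from the Sample size section.** Control change 1.3 points, intervention change 1.04, so the target difference is 1.3 − 1.04 = 0.26. SD of change 2, two-sided alpha 0.05, power 80%, 112 per group before clustering. With the factor 1.03, 112 × 1.03 = 115.4, that is 116 per arm or 232 in total.

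**Assumed input.** r, the correlation of baseline MMSE with 18-month IADL change. The document gives none. I take 0.2 to 0.4 as the working range and show 0.1 to 0.5. If age, education or comorbidities already explain part of that correlation, the gain over the listed covariates is smaller.

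**The plan's own figure first.** n per group = 2 × (1.960 + 0.842)² × 2² / 0.26² = 929, not 112. Power at 112 per group for 0.26 is 16.2%; 112 per group has 80% power only for a difference of about 0.75. The stated sample size therefore does not follow from its stated inputs. That is a separate point, but it means 0.26 is a poor yardstick for what follows.

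**Effect of adjustment.**
- Residual variance falls by r². The equivalent gain in patients is 1/(1 − r²) − 1.
- Unadjusted standard error at 116 per arm: 2 × √(2/116) = 0.263. The 95% half-width is 1.96 × 0.263 = 0.515. Adjusted, it is 0.515 × √(1 − r²).

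**Effect of chance imbalance.**
- The SD of the standardised baseline difference is √(2/116) = 0.131. Its median absolute value is 0.6745 × 0.131 = 0.089 SD, and its 95% limit is 1.96 × 0.131 = 0.257 SD.
- The shift in the estimate is imbalance × r × 2.

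| r | variance cut | equivalent extra patients | half-width, 116 per arm | power for 0.26, 112 per arm | shift at median imbalance | shift at 95% limit |
|---|---|---|---|---|---|---|
| 0 | 0% | 0% | 0.515 | 16.2% | 0 | 0 |
| 0.1 | 1% | 1% | 0.512 | 16.3% | 0.018 | 0.05 |
| 0.2 | 4% | 4% | 0.504 | 16.7% | 0.035 | 0.10 |
| 0.3 | 9% | 10% | 0.491 | 17.4% | 0.053 | 0.15 |
| 0.4 | 16% | 19% | 0.472 | 18.4% | 0.071 | 0.21 |
| 0.5 | 25% | 33% | 0.446 | 20.1% | 0.089 | 0.26 |

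For the 0.75-point difference that 112 per group could detect with 80% power, power rises to 81.6% at r = 0.2 and 86.4% at r = 0.4.

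**The form of the covariate matters.** The test is on the time-by-group interaction. A simulation with 112 per group, visits at 0, 1, 6 and 18 months, complete data, no clustering and 1,500 runs per r gave these standard errors for that term:

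| r | MMSE omitted | MMSE as main effect | MMSE plus MMSE-by-time |
|---|---|---|---|
| 0.2 | 0.252 | 0.252 | 0.246 |
| 0.4 | 0.260 | 0.260 | 0.237 |

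A main effect alone gains nothing. The gain comes from the interaction with time, and it agrees with √(1 − r²): 0.246/0.252 = 0.98 and 0.237/0.260 = 0.91.

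These sizes are for IADL change treated as continuous. No SD is given for DAD-6, so no size can be stated for that scale.

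**The case against.** The strongest reply is that this is an improvement and not an error. Leaving out a prognostic covariate does not invalidate a randomised comparison, the choice of covariates is partly preference, and a journal article may leave such detail to the analysis plan. The Background sentence says only that these factors may matter, and it names several others; by the same logic baseline depression could be asked for. The correlation is assumed, and at r = 0.1 the gain is 1%.

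Most of this stands and sets the size of the point. It does not remove it, because the article prints a specific list, and adjustment for a baseline value already collected costs almost nothing.

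Several stronger readings are tempting, and the document does not support them:

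- **That the result would be biased.** Under proper randomisation it would not be.
- **That imbalance could move the estimate by 40 to 80% of the planned effect.** This takes the 0.10 to 0.21 shift at the 95% limit and divides by 0.26. It is a worst case, and the unadjusted standard error of about 0.26 already reflects it. Adding it to the precision loss counts the same variance twice.
- **That allocating later patients with their referent physician's first patient makes chance imbalance much more likely.** The plan's own factor for this clustering is 1.03, or 3% more variance. Whether a foreseeable arm affects who is enrolled is a separate question of allocation concealment.
- **That diagnosis and stage must also be in the primary model.** It has several categories, and patients enter at a first consultation, when a diagnosis may not be settled.
- **That MMSE and stage will be available for every patient.** Table 1 schedules them but does not promise completeness.

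The planned comparison of baseline characteristics between arms would show an imbalance in MMSE but would not adjust for it.

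**Conclusion.** The point holds as a modest loss of efficiency that is cheap to avoid. The printed covariate list omits a baseline measure that the trial collects and whose domain it names as a risk factor. For an assumed r of 0.2 to 0.4, adjustment would remove 4 to 16% of residual variance and narrow the 95% interval by about 2 to 8% (half-width from 0.515 to 0.504 or 0.472 points). It would also remove a typical chance shift of 0.035 to 0.07 points, roughly 0.13 to 0.27 of a standard error.

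A reader should not infer that adjustment rescues the trial's power. At the stated difference of 0.26 and 112 per group, power moves only from 16.2% to between 16.7% and 18.4%.

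The conclusion rests on the assumed r, on a continuous analysis of change, and on MMSE entering with its interaction with time. The rule of adjusting only for significant covariates would make the gain depend on the data.

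**What to change.** In the primary model, for IADL and DAD-6 alike, prespecify baseline MMSE as a continuous covariate together with its interaction with time. Keep both terms whether or not they are significant. Use only the time-0 value, because later MMSE values are outcomes that the intervention could affect. State a simple rule for missing baseline MMSE that does not depend on study arm, for example imputation from other baseline data.

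Use diagnosis and stage, collapsed to a few broad categories with one for unsettled diagnoses, as a sensitivity adjustment that also enters with time.

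The cost is one or two sentences in the analysis section and no new data collection. MMSE takes two coefficients if time is linear, or four if the four visits are treated as categories (one main effect and three interactions). The change should be fixed before outcome data are examined by arm, since adding cognition afterwards would be open to challenge. The sample-size calculation needs its own correction.
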